#### Standard cardiac rehabilitation

Controls receive the standard cardiac rehabilitation program in accordance with the recommendations for the rehabilitation of coronary heart disease [18]. To ensure that any potential benefits of the cognitive-behavioral rehabilitation program are not due to a longer rehabilitation duration of the cognitive-behavioral program, the standard rehabilitation program is also conducted for four weeks instead of the usual three weeks.

### Outcomes

#### Primary outcome

Our primary outcome is cardiac anxiety 12 months after the end of rehabilitation. Cardiac anxiety is assessed with the German 17-item version of the Cardiac Anxiety Questionnaire [15, 16]. All items are rated from 0 to 4 points (“never” to “always”). Higher values represent more pronounced fear. The total score is calculated as the mean of eight items on fear, four items on avoidance, and five items on attention.

#### Secondary outcomes

##### Mental health

The three subscales of the Cardiac Anxiety Questionnaire, i.e., fear, avoidance, and attention, are collected as secondary outcomes [15, 16]. Furthermore, the level of change in cardiac anxiety and the reduction of cardiac anxiety by at least 0.2 points (5% of the scale range) is assessed. Other indicators of mental health include depression (0 to 27 points), generalized anxiety (0 to 21 points) and somatization (0 to 30 points). These outcomes are assessed using the Patient Health Questionnaire [25].

*Physical health*: Functional capacity is assessed with eight items of the IRES-24 (Indicators of rehabilitation status, German: Indikatoren des Reha-Status). The items assess difficulties in engaging in physical activities, e.g., sports that really make you sweat, such as jogging, skiing, and mountain hiking [26]. Difficulties are assessed on a 5-point scale (“impossible” to “no difficulty”). The total score ranges from 0 to 10 points. Higher values of the total score represent better functional capacity. Additionally, the rehabilitation center records systolic and diastolic blood pressure and ergometer performance in watts per kg at the beginning and end of rehabilitation.

*General health*: To describe general health, we use a visual analog scale with scores ranging from 0 to 100 points [27]. Furthermore, we use the 5-level EQ-5D, a preference-based measure of health-related quality of life, to assess general health [28, 29]. Using the 5-level EQ-5D, participants are asked to indicate their health status by answering questions from five different dimensions: mobility, self-care, usual activities, pain/discomfort, and anxiety/depression. Each dimension has five levels of severity: no problems, mild problems, moderate problems, severe problems, and extreme problems. Each number combination represents a health state, with 11111 reflecting no problems in any of the five dimensions. The 5-digit health status is then converted into an index value reflecting how good or bad an individual’s health status is, according to the preferences of the German general population [30]. The health state of 11111 corresponds to a value of 1.

##### Health behavior

Motivation to change lifestyle is assessed using a 5-point scale ranging from 1 (“certainly”) to 5 (“certainly not”), and we count who is motivated to change lifestyle (certainly or rather yes) [31]. Confidence about regular physical activity is evaluated using the Exercise Self-Efficacy Scale comprising 10 statements (e.g., “I am confident that I can accomplish physical activity and exercise goals that I set”). These statements are rated on a 4-point scale (“not at all true” to “always true”). A total score is calculated ranging from 10 to 40 points [32]. Higher scores represent a stronger belief to engage in regular physical activity. Smoking status is determined by three categories (“yes, I smoke”, “no, but I have smoked”, and “no, I have never smoked”) at baseline and by two categories at the end of the rehabilitation and at the 3-month and 12-month follow-up (“yes” or “no”). Body weight and height are aggregated to the body mass index in kg/m². Weekly physical activity is assessed for a maximum of three activities [33]. Participants state which physical activities were performed in the last four weeks. In addition, they provide the frequency and duration in minutes for each activity. Frequency and duration are multiplied for each activity, the dose of all activities is added up, and the sum is finally divided by four to calculate the weekly amount of physical activity.

##### Work ability and job situation

Self-rated work ability is measured using the Work Ability Score [34]. The Work Ability Score is the first item of the Work Ability Index and compares the current work ability with the lifetime best. The scale ranges from 0 („completely unable to work“) to 10 („work ability at its best”). The Work Ability Score correlates strongly with the total Work Ability Index score [35]. We also assess employment, sick leave status and cumulative sickness absence in the last 3 or 12 months (weeks). At the 3-month and 12-month follow-up, we ask when the participants were first working for at least four weeks without absenteeism (time to sustainable return-to-work) [36], and we assess if patients receive a disability pension. The physician’s assessment of work capacity for the last job and the general labor market at the end of rehabilitation are extracted from the standardized medical discharge reports [37].

##### Dose delivered

The dose delivered describes the number of intended intervention units provided to participants [38]. Treatments during the rehabilitation program are extracted from the participants’ standardized medical discharge reports, which document all treatments performed during rehabilitation using the classification of therapeutic services [39].

##### Dose received

The dose received describes the elements of the intervention the participants actually received [38]. We record the dose of the cognitive-behavioral rehabilitation received using three scores, which we used in a previous study evaluating the implementation of the approach [14]. These patient-reported experience measures assess the content of the cognitive-behavioral rehabilitation program (12 items, 0 to 12 points), the consistency of the approach (4 items, 0 to 16 points), and the gain in competence experienced by the participants (10 items, 0 to 40 points).

##### Health-related costs

For our health economic evaluation, we use the Questionnaire for Health-Related Resource Use in an Elderly Population [40]. The questionnaire assesses, among others, the type of health insurance, medications taken in the last seven days, outpatient physician visits and therapeutic services used in the last 3 months, as well as rehabilitation measures, outpatient surgery and treatments in outpatient or inpatient hospitals in the last 12 months. The health-related costs are calculated using the rates proposed by Bock et al. [41].

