What (procedures)	The seven sessions cover, amongst others, mindfulness exercises, the ACT matrix, acceptance of negative thoughts, mental flexibility, personal values, and the elaboration of concrete plans for the time after rehabilitation. A more detailed overview of the seven sessions is presented in Additional File 2.	During the admission interview, anamnestic information (including contextual factors such as family, work, and biography) as well as the experience of illness and illness behavior are recorded, and the expectations of the rehabilitation patients are clarified. In addition, at the end of rehabilitation, mental disorders are assessed with a standardized short interview in order to specify further treatment recommendations.	Participants learn progressive muscle relaxation and develop individual ways to apply the technique in everyday life.	The following topics will be covered in the two sessions. Session 1: Structure and function of the heart and cardiovascular system; function of the autonomic nervous system and the hormonal system. Session 2: Control function of the brain and influence of the emotional state; influence of lifestyle and attitude changes on physical processes, especially on the cardiovascular system.	The exercise intervention includes an individual admission assessment by a physical therapist, cardiovascular exercise therapy, ergometer training, strength training, and coordination training in a group.
Who provided	A psychological psychotherapist or graduated psychologist in psychotherapy training leads the group throughout the rehabilitation and is the primary psychological contact. The primary physical therapist is present at the first and last group meetings.	Psychological psychotherapist or graduated psychologist in psychotherapy training	Psychological psychotherapist or graduated psychologist in psychotherapy training	Physician	The primary physiotherapist leads the group exercise sessions throughout rehabilitation.
How	Group intervention	Individual intervention	Group intervention	Group intervention	Group intervention
Where	Quiet group room	Workroom of the primary psychologist	Quiet group room/gym	Quiet group room in the rehabilitation facility	Gym

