Treatments during the rehabilitation program	Standardized medical discharge report [37], coding according to the classification of therapeutic services report [39]	Continuously, minutes or hours	T1
Content of the cognitive-behavioral rehabilitation program	[14]	Continuously, 0 to 12 points	T1
Consistency of the approach	[14]	Continuously, 0 to 16 points	T1
Gain in competence	[14]	Continuously, 0 to 40 points	T1
Recommendations for subsequent services	Standardized medical discharge report [37]	Binary, yes/no for 12 subsequent services	T1
Utilization of medical and non-medical services	FIMA [40]	Continuously, resource usage in euro	T3
Diagnoses	Standardized medical discharge report [37], clinical interview[42]	Nominal	T1
Sociodemographic data	Own development	Various (native language, number of children, level of school education, vocational qualification)	T0

*BSA-F* Physical Activity, Exercise, and Sport Questionnaire (German: Bewegungs- und Sportaktivität Fragebogen), *CAQ* Cardiac Anxiety Questionnaire, *ESES* Exercise Self-Efficacy Scale, *EQ-5D* European Quality of Life 5 Dimensions, *FIMA* Questionnaire for Health-Related Resource Use in an Elderly Population (German: Fragebogen zur Erhebung von Gesundheitsleistungen im Alter), *IRES-24* Indicators of rehabilitation status (German: Indikatoren des Reha-Status), *OutCaRe* Outcome of Cardiac Rehabilitation, *PHQ-D* Patient Health Questionnaire, *T0* Beginning of the rehabilitation, *T1* End of the rehabilitation, *T2* 3-month follow-up, *T3* 12-month follow-up

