### Data collection methods

Data are collected via questionnaires, clinical examinations, and the standardized rehabilitation discharge reports. Questionnaires are completed at four measurement points: at the beginning and end of rehabilitation, as well as 3 and 12 months after completion of rehabilitation. The assessments have already been tested during the implementation of the intervention [14] and are described in detail above (Table 2). The 3-month and 12-month follow-up questionnaires are sent from the rehabilitation center. Patients whose follow-up questionnaires have not been received after two weeks are reminded twice at two-week intervals, if necessary. We enclose the questionnaire again with each reminder. Clinical examinations are performed at the beginning and end of rehabilitation. Treatments administered during rehabilitation are documented by the rehabilitation center in the discharge reports at the end of rehabilitation.

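### Outpatient visits, therapies and medication are asked about once, at month 12, with 3-month or 7-day recall, so the cost-effectiveness analysis must extrapolate most of the year in these categories

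*Protocol article*

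**What the plan says.** The Health-related costs section of the protocol article names the FIMA as the source for the health economic evaluation. It gives two sets of recall periods in one sentence. The short ones are for "medications taken in the last seven days, outpatient physician visits and therapeutic services used in the last 3 months". The sentence then continues with the long ones: "as well as rehabilitation measures, outpatient surgery and treatments in outpatient or inpatient hospitals in the last 12 months".

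Table 2 gives the schedule: "Utilization of medical and non-medical services FIMA [40] Continuously, resource usage in euro T3". No other row of Table 2 records service use or medication after discharge. Questionnaires as such are completed "at the beginning and end of rehabilitation, as well as 3 and 12 months after completion of rehabilitation" (Data collection methods), so a 3-month form (T2) is already sent, but without these items.

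Three other places bear on the point:

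- Table 1, individual psychological sessions, states for the intervention programme that "at the end of rehabilitation, mental disorders are assessed with a standardized short interview in order to specify further treatment recommendations". The Diagnoses section likewise places the structured clinical interview in the intervention group and describes none for controls.
- Recommendations for 12 subsequent services are extracted from the discharge report at the end of rehabilitation. No item is listed that records whether they were taken up. The discharge report documents treatment during rehabilitation only (Dose delivered).
- Statistical methods commits to an incremental cost-effectiveness ratio from a societal perspective, with quality-adjusted life years derived from the 12-month EQ-5D assessment and a bootstrap confidence interval.

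**The concern.** With a single administration at month 12, a 3-month recall reaches back to about month 9 and a 7-day recall to the last week of the year. Whatever participants used earlier in these categories is not collected, and no analysis plan can recover it. Any 12-month cost for outpatient visits, therapeutic services and medication must be extrapolated from the end of the year.

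That matters most if use changes over the year and the pattern differs between arms. The design gives a reason to allow for this: only the intervention arm is described as having a discharge interview meant to feed treatment recommendations. If early use differs by arm, the extrapolation error does not cancel in the cost difference, which is the numerator of the cost-effectiveness ratio. The bootstrap interval would not show it, because it reflects sampling error and not unobserved time.

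A second, descriptive loss is that the trial could not report by arm how much outpatient care followed discharge in the first nine months. That would help in interpreting a 12-month difference.

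**Working it through.** The protocol gives no figure for coverage or annualisation, so there is none to reproduce. The sample-size figures play no part here.

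**Step 1: coverage of the 12 months after discharge.** Inputs are the recall periods (Health-related costs) and the T3-only schedule (Table 2). The form is assumed to be answered at month 12. Coverage = recall period / 12 months.

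| Category | Recall | Coverage of the year | Coverage of months 0–9 |
|---|---|---|---|
| Outpatient visits, therapeutic services | 3 months | 3/12 = 25% | 0% |
| Medication | 7 days | 7/365.25 = 1.9% | 0% |
| Rehabilitation, outpatient surgery, hospital treatment | 12 months | 12/12 = 100% | 100% |

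**Step 2: what simple scaling would recover.** Both the shape and the scaling factor are assumptions, because the protocol states neither. Let the monthly rate move linearly from r at discharge to 1 at month 12.

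- Mean rate over the year = (r + 1)/2.
- Mean rate over months 9–12 = rate at month 10.5 = 1 + (r − 1) × 1.5/12.
- Share recovered by four times last-quarter use = second line / first line.

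Results:

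- r = 1.5: 1.0625/1.25 = 85%
- r = 2: 1.125/1.5 = 75%
- r = 3: 1.25/2 = 62.5%
- r = 0.5 (use rises): 0.9375/0.75 = 125%

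The last line shows that the error changes sign if use rises over the year. These percentages describe visits and therapeutic services, not total cost. Medication rests on one week, so its extrapolation is longer still.

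**Step 3: effect on a difference between arms.** If both arms follow the same proportional pattern, the difference is scaled by the same factor as the totals. If they do not, the distortion can be larger. Suppose one arm is flat at rate 1 (12 units in the year) and the other falls from 2 to 1 (12 × 1.5 = 18 units). The true difference is 6. Scaling the last quarter gives 4 × 3 × 1.125 = 13.5 against 12, a difference of 1.5. Which arm is favoured depends on which has the early excess, and the protocol does not say.

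**Step 4: what a 3-month form would add.** A 3-month recall at T2 covers months 0–3. With T3, observed time for visits and therapies rises from 3/12 to 6/12 = 50%, leaving months 3–9 to interpolate. If use is monotone over the year, the true rate in months 3–9 lies between the T2 and T3 rates. Filling those six months once with each rate therefore brackets the true annual total. With T3 alone no such bracket exists.

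**The case against.** Several points on the other side stand.

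- **Scope.** A reader who stops at the short recall periods might infer that all treatment in the first nine months goes unobserved. It does not: the same sentence gives 12-month recall for rehabilitation measures, outpatient surgery and hospital treatment. Sickness absence is also collected at T2 and T3 over 3 or 12 months.
- **Direction.** A reader might infer that the cost difference is biased in favour of the intervention. That needs use to fall over the year and the early excess to lie in the intervention arm. The protocol gives no timing of uptake. Discharge recommendations are extracted at T1 without restriction to one arm, so a difference in recommendations, though not in uptake, can be seen.
- **Size.** The share of total cost in the short-recall categories is not given, so the effect on the ratio cannot be derived.
- **Method.** Multiplying by four is not in the article. How annual costs are derived may be set out in an analysis plan that is not shown.
- **Primary outcome.** A reader might infer that unrecorded aftercare undermines the cardiac anxiety result. It does not. Care that follows from the programme is a consequence of allocation and belongs to the randomised contrast.
- **Remedy.** Half the year stays unobserved, medication would still rest on two single weeks, and a longer T2 form could cost some response.

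What does not stand is that this can be left to the analysis. An analysis plan can choose how to extrapolate, but it cannot supply early use that the schedule never collects.

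**Conclusion.** The point holds for three categories: outpatient physician visits, therapeutic services and medication. About 25% of the follow-up year is observed for the first two and about 2% for the third, and all of it lies at the end. The planned cost-effectiveness analysis must extrapolate the rest, while the design contains an arm-specific reason why early use might differ.

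The coverage figures follow directly from the protocol and assume only that the T3 form is answered at month 12. The recovery figures of 85%, 75% and 62.5% are illustrations. They depend on an assumed linear decline and an assumed four-fold scaling, and apply only within the short-recall categories. The size and direction of any bias in the cost difference are unknown.

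This is a limitation of a secondary, prespecified economic analysis that can be reduced cheaply. It is not a contradiction in the protocol, and the randomised comparison of cardiac anxiety at 12 months is not affected.

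**What to change.** Add the short-recall FIMA items (outpatient physician visits and therapeutic services in the last 3 months, medication in the last 7 days) to the existing T2 questionnaire in both arms.

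Compute 12-month cost in these categories from T2 and T3, with months 3–9 interpolated. As a sensitivity analysis, fill months 3–9 once at the T2 rate and once at the T3 rate, and report the cost-effectiveness result under each. Impute T2 values for participants already past month 3 with the planned chained equations. Report outpatient care and medication by arm at T2 and T3.

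The cost is a short amendment and a few more items on a form that is already posted. The downsides are a slightly longer T2 form with a possible small effect on response, missing T2 values for participants already past that point (recruitment has started), and a middle six months that is still interpolated.

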##### Recommendations for subsequent services

Recommendations for 12 common subsequent services are extracted from the standardized medical discharge report at the end of the rehabilitation [37].

##### Diagnoses

Diagnoses are also extracted from the standardized medical discharge report at the end of the rehabilitation [37]. In the intervention groups mental disorders are assessed using a structured clinical interview [42].

##### Sociodemographic data

These include data on native language, partnership, number of children, level of school education and vocational qualification.

Table 2 summarizes all outcomes, measurement instruments and the timing of the assessments.

**Table 2 Tab2:** Measures, assessment, expected scaling, and measurement occasions

*Outcome*	*Source and reference*	*Scaling*	*Time*
**Primary outcome**			
Cardiac anxiety	Total score of the German 17-item version of the CAQ [16]	Continuously, 0 to 4 points	T0, T1, T2, T3
**Secondary outcomes**			
Fear	Subscale of the German 17-item version of the CAQ [16]	Continuously, 0 to 4 points	T0, T1, T2, T3
Avoidance	Subscale of the German 17-item version of the CAQ [16]	Continuously, 0 to 4 points	T0, T1, T2, T3
Attention	Subscale of the German 17-item version of the CAQ [16]	Continuously, 0 to 4 points	T0, T1, T2, T3
Change in score for cardiac anxiety	Total score of the German 17-item version of the CAQ [16]	Continuously, − 4 to 4 points	T1, T2, T3
Decrease in cardiac anxiety by 0.2 points	Total score of the German 17-item version of the CAQ [16]	Binary, yes/no	T1, T2, T3
Depression	PHQ-D [25]	Continuously, 0 to 27 points	T0, T1, T2, T3
Generalized anxiety	PHQ-D [25]	Continuously, 0 to 21 points	T0, T1, T2, T3
Somatization	PHQ-D [25]	Continuously, 0 to 30 points	T0, T1, T2, T3
Functional capacity	IRES-24 [26]	Continuously, 0 to 10 points	T0, T1, T2, T3
Blood pressure	Clinical examination	Continuously, systolic/diastolic in mmHg	T0, T1
Endurance	Clinical examination	Continuously, ergometer performance in watts/kg	T0, T1
General health	Visual analog scale of the EQ-5D [27]	Continuously, 0 to 100 points	T0, T1, T2, T3
Health-related quality of life	EQ-5D [28]	Continuously, health state of 11111 corresponds to a value of 1	T0, T1, T2, T3
Motivation to change lifestyle	OutCaRe [31]	Binary, certainly or rather yes vs. uncertain or less	T0, T1
Weekly physical activity	BSA-F [33]	Continuously, minutes	T0, T1, T2, T3
Self-efficacy to exercise	ESES [32]	Continuously, 10 to 40 points	T0, T1, T2, T3
Smoking status	Own development	Binary, yes/no	T0, T1, T2, T3
Weight	Clinical examination	Continuously, body mass index in kg/m²	T0, T1, T2, T3
Self-rated work ability	Work Ability Score [34]	Continuously, 0 to 10 points	T0, T1, T2, T3
Sickness absence	Own development	Binary, yes/no	T0, T2, T3
Sickness absence duration	Own development	Continuously, cumulative sickness absence in the last 3 or 12 months in weeks	T0, T2, T3
Stable return to work	[36]	Binary, yes/no	T2, T3
Time to stable return to work	[36]	Continuously, weeks	T2, T3
Employment	Own development	Binary, yes/no	T0, T2, T3
Disability pension	Own development	Binary, yes/no	T0, T2, T3
Capacity for last job	Medical assessment, standardized medical discharge report [37]	Binary, at least six hours per day or less than six hours per day	T1
Capacity for other job	Medical assessment, standardized medical discharge report [37]	Binary, at least six hours per day or less than six hours per day	T1
Treatments during the rehabilitation program	Standardized medical discharge report [37], coding according to the classification of therapeutic services report [39]	Continuously, minutes or hours	T1
Content of the cognitive-behavioral rehabilitation program	[14]	Continuously, 0 to 12 points	T1
Consistency of the approach	[14]	Continuously, 0 to 16 points	T1
Gain in competence	[14]	Continuously, 0 to 40 points	T1
Recommendations for subsequent services	Standardized medical discharge report [37]	Binary, yes/no for 12 subsequent services	T1
Utilization of medical and non-medical services	FIMA [40]	Continuously, resource usage in euro	T3
Diagnoses	Standardized medical discharge report [37], clinical interview[42]	Nominal	T1
Sociodemographic data	Own development	Various (native language, number of children, level of school education, vocational qualification)	T0

*BSA-F* Physical Activity, Exercise, and Sport Questionnaire (German: Bewegungs- und Sportaktivität Fragebogen), *CAQ* Cardiac Anxiety Questionnaire, *ESES* Exercise Self-Efficacy Scale, *EQ-5D* European Quality of Life 5 Dimensions, *FIMA* Questionnaire for Health-Related Resource Use in an Elderly Population (German: Fragebogen zur Erhebung von Gesundheitsleistungen im Alter), *IRES-24* Indicators of rehabilitation status (German: Indikatoren des Reha-Status), *OutCaRe* Outcome of Cardiac Rehabilitation, *PHQ-D* Patient Health Questionnaire, *T0* Beginning of the rehabilitation, *T1* End of the rehabilitation, *T2* 3-month follow-up, *T3* 12-month follow-up

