### Statistical methods

We will analyze short-term (end of rehabilitation and 3-month follow-up) and long-term effects (12-month follow-up) using different models and publish the findings separately. We will use mixed models if more than one measurement point needs to be considered, i.e., end of rehabilitation and 3-month follow-up, and generalized linear models otherwise. If baseline scores are available, these will be included as a covariate when estimating the treatment effect. If outcomes are binary, a logit link will be used. High depression, high generalized anxiety, and high cardiac anxiety, as well as age, sex, and education, are tested as possible moderators of the treatment effect on our primary outcome cardiac anxiety assessed at the 12-month follow-up.

For health economic evaluation, we will calculate an incremental cost-effectiveness ratio [44]. Assessments of costs employ a societal perspective [41, 45]. Effectiveness is measured using quality-adjusted life years as derived from the 12-month assessment of the EQ-5D-5 L [28, 30]. The incremental cost-effectiveness ratio is calculated by dividing the difference in costs between both interventions by the difference in effectiveness between both interventions. Bootstrapping is used to compute a 95% confidence interval of the incremental cost-effectiveness [44].

Missing data will be imputed using chained equations [46]. We will create 20 independent data sets with complete values. Parameter estimates of the models will be combined in accordance with Rubin’s rules [47]. Statistical tests will be regarded as significant if the two-sided p-value of a test is less than 0.05. An up-to-date version of Stata (StataCorp, College Station, Texas, USA) will be used to conduct the analyses.

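### Time to stable return to work is scaled as continuous weeks and given no event or censoring treatment, so patients not back at work are dropped or given imputed return times

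*Protocol article*

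**What the plan says.** The section on work ability and job situation says that patients are asked, at the 3-month and 12-month follow-up, when they first worked for a spell of at least four weeks without absence. Table 2 turns this into two secondary outcomes, both at T2 and T3:

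- "Stable return to work", binary.
- "Time to stable return to work", scaled as "Continuously, weeks".

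The same section also states that "we assess if patients receive a disability pension".

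Statistical methods gives one rule for all outcomes: "We will use mixed models if more than one measurement point needs to be considered", meaning the end of rehabilitation and 3 months, "and generalized linear models otherwise". The only exception by type of outcome is a logit link for binary outcomes. Then: "Missing data will be imputed using chained equations", with 20 completed data sets. Short-term and long-term effects are analysed with different models and published separately.

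Time to return is not collected at the end of rehabilitation. By the protocol's own rule it therefore has one measurement point in each report and falls to a generalized linear model both times. No event indicator, censoring rule or time-to-event model is mentioned.

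**The concern.** The binary return item and the disability pension item show that the protocol itself expects some patients not to return. For them the time is not an unanswered question. It is absent because the event has not happened yet, so it is right-censored. A continuous-weeks variable has no place for that, and the stated rules leave two routes:

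- **Exclusion.** The arms are compared among returners only, a group formed after randomisation and possibly by the treatment itself.
- **Imputation.** Chained equations borrow from patients who did return and give non-returners a return time.

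The 3-month assessment is hit harder. Three months is about 13 weeks and the spell must last four, so a return starting after about week 9 (13 − 4) cannot yet be confirmed.

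The Study setting section says that this rehabilitation is meant to prevent health-related exit from work and disability pensions, and the Discussion says that the results are to inform pension insurers. A time-to-return result that is too small, or points the wrong way, would reach the readers most likely to use it.

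**Working it through.** **The protocol's own figures.** It gives none for return to work. Its sample size concerns cardiac anxiety and reproduces. A t-test with difference 0.2 and SD 0.6 needs 142.25, so 143 per arm or 286. Then 143/0.7 = 204.3, so 205 per arm or 410, and power with 205 per arm is 0.92. Nothing below changes this.

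**Quantities compared.** Let p be the proportion returned by week 52 and m the mean time among returners.

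- Returners-only difference: m(intervention) − m(control).
- Restricted mean time not in stable work: R = p·m + (1 − p)·52, which keeps every patient.

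All return rates and times below are assumptions.

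**1. The programme adds late returners.** Control: 60% return, mean 10 weeks, so R = 0.6×10 + 0.4×52 = 26.8.

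| Intervention arm | Returners-only difference | Restricted-mean difference |
|---|---|---|
| 60% at 10 weeks plus 10% at 30 | (6 + 3)/0.70 − 10 = +2.86 | 6 + 3 + 15.6 − 26.8 = −2.2 |
| 60% at 8 weeks plus 10% at 30 | (4.8 + 3)/0.70 − 10 = +1.14 | 4.8 + 3 + 15.6 − 26.8 = −3.4 |
| 60% at 10 weeks plus 5% at 30 | (6 + 1.5)/0.65 − 10 = +1.54 | 6 + 1.5 + 18.2 − 26.8 = −1.1 |
| 70% at 8 weeks, none late (contrast) | 8 − 10 = −2.0 | 5.6 + 15.6 − 26.8 = −5.6 |

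A different control pattern behaves the same way. Take 65% of controls returning evenly over weeks 2 to 20 (mean 11), and a further 10% in the intervention arm returning over weeks 30 to 50 (mean 40). The returners-only difference is (0.65×11 + 0.10×40)/0.75 − 11 = +3.87 weeks. The restricted-mean difference is −0.10×(52 − 40) = −1.2 weeks.

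*When the sign turns.* If early returners are unchanged, any extra returner slower than the control mean raises the returners-only mean. If early returners are also two weeks faster, as in row 2, the extra 10% must return later than week 22, because 0.6×8 + 0.1×22 = 0.7×10.

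**2. The imputation route.** The four table rows were simulated with 205 per arm, all questionnaires returned, 500 replicates and 20 normal-regression imputations of time on arm. The imputed differences were +2.90, +1.07, +1.56 and −2.04 weeks, equal to the simulated returners-only differences in every row. The simulated restricted-mean differences were −2.15, −3.47, −1.12 and −5.63. Imputation centres non-returners on the returners of their own arm. Further covariates could shift the imputed values, but no time is observed among non-returners to correct them.

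**3. Proportional (constant) hazards.** With λ = −ln(1 − p)/52, the returners' mean is 1/λ − 52(1 − p)/p and the restricted mean is p/λ.

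Example with 60% of controls returning and hazard ratio 1.3:

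- Control: λ = 0.01762, returners' mean 22.08, restricted mean 34.05.
- Intervention: λ = 0.02291, p = 0.696, returners' mean 20.96, restricted mean 30.39.
- Differences: −1.13 against −3.66, a ratio of 31%.

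| Control return by week 52 | Hazard ratio | Returners only | Restricted mean | Ratio |
|---|---|---|---|---|
| 40% | 1.3 | −0.65 | −2.72 | 24% |
| 40% | 1.5 | −1.08 | −4.39 | 25% |
| 60% | 1.3 | −1.13 | −3.66 | 31% |
| 60% | 1.5 | −1.86 | −5.79 | 32% |
| 70% | 1.3 | −1.43 | −3.96 | 36% |
| 70% | 1.5 | −2.34 | −6.17 | 38% |

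The sign never changes here. A 13-week horizon with the same return proportions gives the same ratios.

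**The case against.** The strongest reply is that this is a condensed article. It nowhere says how a non-returner's time is coded or that it counts as missing. Table 2 describes measures and expected scaling, not models. It also lists event status next to time, which are the two inputs a survival analysis needs. It is true that both routes, exclusion and imputation, are inferred from the general rules. But the article is not silent: it fixes a scale and a model class for its outcomes, and nothing exempts this one or says that the two rows are analysed together.

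A reader might infer that generalized linear models cannot deal with censored times at all. That goes too far. A Poisson model with an exposure offset, or a discrete-time logit or complementary log-log model, can do so. Each needs event status and time at risk as its input, however, not a single continuous-weeks variable.

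Other outcomes would give some warning. Binary return, cumulative sickness absence and employment are all collected at both follow-ups. In the first late-returner case the binary outcome would show 70% against 60%. That would reveal a conflict, but the time result itself would still be wrong.

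Publishing short-term and long-term effects separately is a deliberate choice and not a fault in itself.

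**Conclusion.** The point holds. The stated scale and models do not fit an outcome that some patients will not have reached, and the stated rules lead to exclusion or imputed return times. Under proportional hazards with the assumed return rates, roughly a quarter to two fifths of the restricted-mean difference remains.

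A reader might infer that the trial's return-to-work effect will come out reversed. The documents do not support that. They give no return rates or timings, reversal needs additional returners who come back late, and it did not occur under proportional hazards or in the case without late returners. Nor do the documents state that non-returners will be treated as missing; that is how the general rule would apply to them.

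This concerns one secondary outcome. It should be corrected before analysis, but the primary result does not depend on it.

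**What to change.** - Change the Table 2 scaling of this outcome to time to event, with the planned binary stable-return item as event indicator and the reported time of first return as the time.
- In the 12-month report, analyse one event history from the end of rehabilitation. Censor non-returners at their last returned questionnaire. Show Kaplan-Meier curves and estimate the effect with a Cox model or the 52-week restricted mean.
- The separate short-term report may stay, with censoring at 3 months.
- State that no return time is imputed for patients known not to have returned.
- Define the at-risk population, in particular how patients already working or not employed at baseline are handled. Employment and sickness absence are recorded at T0.
- State whether the time runs to the start or the completion of the four-week spell, so that the censoring date matches.
- Treat disability pension as a competing event in a sensitivity analysis, dated only to the interval between questionnaires because it is recorded as yes or no. Include death only where known, since it is not a listed outcome.

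Cost: one Table 2 entry, a few sentences and slightly more analysis work. The main analysis needs no new data, because return status and time of first return are already collected. The competing-event analysis is limited by the missing dates.
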